Antibiotic use can be improved by using educational interventions such as dissemination of printed and audio-visual educational materials, group education, personal or group feedback, individual outreach visits, reminders at the time of prescribing, and computer-assisted decision-making systems, among others, but these interventions generally result in little change in prescription practices, although the effect is greater with multi-faceted approaches [7, 8]. In a recent Cochrane review of systematic reviews aimed at assessing the effects of interventions targeting clinician antibiotic prescribing for ALRTIs in primary care, the reviewers found that the most powerful tools for reducing unnecessary antibiotic prescribing are C-reactive protein (CRP) rapid testing, shared decision making, and procalcitonin-guided management without compromising outcomes of patient satisfaction and re-consultation, although the measurement of these outcomes was limited in the trials [9].

The antibiotic prescribing behaviour of GPs for acute cough in adults is influenced by their perceptions of patient expectations, but sometimes their perceptions do not match patient views [10]. Patients report lower levels of satisfaction with their consultation if they have an expectation for antibiotics that is not met, and being able to effectively elicit patient views towards shared decisions is therefore an important skill for clinicians managing acute cough. Interactive workshops for healthcare professionals and education of patients are likely to lower the rate of antibiotic prescribing [10]. A Dutch study found that the training of physicians in advanced communication skills by seminar role-playing and peer feedback on consultation transcripts reduced antibiotic prescribing rates by 20% [11]. In a Welsh study a 4% reduction in global antibiotic use was found after web-based training in advanced communication skills [12].

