### Outcome measures

During the index consultation GPs will document the duration of the illness, the severity of cough and other symptoms (rated 0, not problematic; to 6, severely problematic), and the severity of the infections. After randomisation a more detailed case report form (CRF) will be used in the follow-up consultations and will include the same details as the index form plus medical history, current medications, smoking status, findings of structured examination, whether CRP is tested, and whether the booklet is used. The primary outcome measures will be antibiotic consumption within the first 6 weeks, as documented in the CRFs and double-checked by the Pharmacy Unit of the Catalan Institute of Health, which can track if the antibiotic has been dispensed at any of the Catalan pharmacies; the duration of moderate to severe cough (i.e., those rating their cough as 3 or more by means of a Likert scale); and the quality-adjusted life-years (QALYs), which will be collected by means of the EQ-5D-5L questionnaire within the first 6 weeks (Table 1).

**Table 1 Tab1:** Schedule of enrolment, interventions and assessments for the clinical trial

Time point	Study period November 4, 2019–April 30, 2021		
	Day 1	Week 2	Week 6
Enrolment			
Medical history and physical examination	X		
Explanation of the study and informed consent	X		
Initial CRF	X		
Giving out of the symptom diary, up to week 2	X		
Interventions			
CRP rapid test if needed (only among those patients visited by professionals assigned to the CRP intervention groups)*	X		
Use of an interactive booklet (only among those patients visited by professionals assigned to the enhanced communication skill intervention groups)*	X		
Assessments			
Assessment of the clinical outcome		X	X
Collection and review of the symptom diary		X	
EQ-5D-5L questionnaire	X	X	X
Antibiotic consumption	X	X	X
Use of drugs other than antibiotics	X	X	X
Tests ordered by clinicians	X	X	X
Patient satisfaction with care		X	X
Patient perception of the usefulness of the information received		X	X
Patient future consulting intentions		X	X
Absenteeism	X	X	X
Evaluation of adverse events		X	X
Number of re-consultations to primary and secondary care and number of complications regarding the ALRTI			X

*Abbreviations: ALRTI* acute lower respiratory tract infection, *CRF* case report form, *CRP* C-reactive protein, *GP* general practitioner

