Randomisation will take place 2 weeks before initiating the clinical trial (October 21, 2019). Workshop for GPs and nurses assigned to any of the three intervention arms at the end of October 2019

*Monthly internet-based short training capsules for GPs and nurses assigned to any of the intervention groups

Secondary outcome measures are listed in Table 2. The duration of symptoms rated moderate to severe will also be recorded. Because this study will follow patients for 6 weeks, we will be able to better define the duration of acute cough due to ALRTI. Symptoms will be rated daily as 0 (no problem) to 6 (as bad as it could be) until they resolve, and the information will be reported by patients in self-completed diaries, similar to what was done in a recent clinical trial on delayed antibiotic prescribing carried out in Catalonia [18]. For patients who do not return diaries, a short form asking about the details of the duration and severity of symptoms and whether antibiotics have been taken or whether the booklet has been used will be completed by telephone call to the patient.

**Table 2 Tab2:** Secondary objectives and outcome measures

Objectives	Outcome measures	Time point(s) of evaluation of this outcome measure
Number of re-consultations to primary and secondary care and number of complications regarding the ALRTI	Re-consultation for new or worsening symptoms, new signs, or hospital admission, assessed by review of medical notes (practice staff, the local study team, or both using a standard form to report these data), and number of complications regarding the ALRTI	First 6 weeks post-randomisation
Duration of moderate to severe symptoms	Number of days until the last day any of the symptoms is rated 3 or more. Symptoms will be rated daily as 0 (no problem) to 6 (as bad as it could be) until they resolve, and the information will be reported by patients in self-completed diaries.	First 6 weeks post-randomisation
Antibiotic prescription at the baseline visit, differentiating immediate and delayed antibiotic prescribing, and antibiotic dispensing at the pharmacies	Reported in the CRF. The number of patients treated with immediate and delayed antibiotic prescribing will be evaluated. Dispensing of the antibiotics at the pharmacies.	Baseline visit. The dispensing of antibiotics will be tracked in the first 6 weeks post-randomisation.
Drugs other than antibiotics	Reported by patients in self-completed diaries	First 6 weeks post-randomisation

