Tests ordered by clinicians	Reported in the CRF	Baseline visit
Patient satisfaction with care	Reported in the symptom diaries	First 6 weeks post-randomisation
Patient perception of the usefulness of the information received	Collected in the symptom diaries	First 6 weeks post-randomisation
Patient future consulting intentions	Collected in the symptom diaries	First 6 weeks post-randomisation
Serious adverse events	Assessed by review of medical notes (practice staff, the local study team, or both using a standard form to report these data)	First 6 weeks post-randomisation
Number of days of sick leave (absenteeism)	Collected in the CRFs	First 6 weeks post-randomisation

*ALRTI* acute lower respiratory tract infection, *CRF* case report form

The data collection process and the rest of the study procedures will be supervised. A clinical research associate will perform periodic visits to the sites and provide online supervision of the data. A data monitoring committee has been deemed not necessary because of the study characteristics, as well as external audits. Nevertheless, the coordinating team will hold periodic meetings, and study procedures will be reviewed.

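### Three patient-view secondary outcomes have the symptom diary as their only named source, and the telephone form described for diary non-returners leaves them out; their week 6 source is also unclear

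*Protocol article*

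**What the plan says.** All of this is in the Outcome measures section of the protocol article.

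- **Source of the three items (Table 2).** Satisfaction with care is "Reported in the symptom diaries". Perceived usefulness of the information and future consulting intentions are each "Collected in the symptom diaries". The time frame for all three is the first 6 weeks, and no other source is named.
- **Fallback (text before Table 2).** When a diary does not come back, the plan provides for a call to complete "a short form asking about the details of the duration and severity of symptoms and whether antibiotics have been taken or whether the booklet" was used. The list covers symptom duration and severity, antibiotics taken and booklet use.
- **Schedule (Table 1).** The diary entry reads "Giving out of the symptom diary, up to week 2", and collection and review of the diary is marked at week 2 only. The three patient-view items are marked at week 2 and again at week 6.

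**The concern.** The call is aimed at exactly those patients whose diary is missing. For symptoms, which are "reported by patients in self-completed diaries", it provides a second source. For the three patient-view items it does not, although the diary is the only source that Table 2 gives for them.

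The loss need not be neutral. The Background says: "Patients report lower levels of satisfaction with their consultation if they have an expectation for antibiotics that is not met". The interventions aim to lower prescribing from 60% to 45% (Sample size calculation), and GPs and patients cannot be masked (Trial interventions). A link between satisfaction, arm and diary return is therefore plausible. The Background also notes that satisfaction was measured only to a limited extent in earlier trials, so this trial has reason to measure it completely. An answer that was never collected cannot be recovered by a later analysis plan.

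**Working it through.** **1. Comparison of the texts.** The protocol states no diary return rate, so there is no figure of its own to reproduce on this point.

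| Item | Diary | Other named source | On the telephone form |
|---|---|---|---|
| Symptom duration and severity | yes | CRF at the index consultation and at follow-up consultations | yes |
| Antibiotics taken | not needed | CRF, checked against pharmacy dispensing | yes |
| Booklet use | not needed | follow-up CRF | yes |
| Satisfaction, usefulness, consulting intentions | yes | none | not listed |

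The call repeats two items that are held elsewhere and omits three that are not.

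**2. Number of patients.** 2940 / 4 = 735 per arm. Assumed non-return of 5%, 12%, 20% or 40% leaves about 37, 88, 147 or 294 patients per arm without these items. The 12% drop-out in the sample size section is not a diary return figure; it is used here only as one value in the range.

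**3. Return depends on satisfaction, equally in all arms.** All inputs are assumptions: true dissatisfaction p = 20% in usual care and 30% in an intervention arm; return rate r_d among dissatisfied and r_s among satisfied patients.

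Observed rate = p·r_d / [p·r_d + (1 − p)·r_s]

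- r_d = 0.5, r_s = 0.8: 0.10/0.74 = 13.5% and 0.15/0.71 = 21.1%. The difference is 7.6 points, and 26% of usual-care answers are lost.
- r_d = 0.7, r_s = 0.9: 0.14/0.86 = 16.3% and 0.21/0.84 = 25.0%. The difference is 8.7 points, and 14% of usual-care answers are lost.
- r_d = r_s: no bias.

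For the odds ratio, r_d/r_s cancels:

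- True: (0.30/0.70)/(0.20/0.80) = 1.714
- Observed at 0.5/0.8: (0.15/0.56)/(0.10/0.64) = 1.714
- Observed at 0.7/0.9: (0.21/0.63)/(0.14/0.72) = 1.714

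**4. The dependence differs by arm.** Observed OR = true OR × (r_d/r_s in the intervention arm) / (r_d/r_s in usual care). Take r_s = 0.85 in both arms.

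- r_d = 0.6 in usual care and 0.5 in the intervention arm: 1.714 × 0.5/0.6 = 1.43.
- The reverse, 0.5 and 0.6: 1.714 × 0.6/0.5 = 2.06.

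The bias can go either way.

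**5. What the call could recover.** Assume it reaches 70% of non-returners and asks the items. Each return rate r becomes r + 0.7(1 − r).

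- 0.5/0.8 becomes 0.85/0.94: 0.170/0.922 = 18.4% and 0.255/0.913 = 27.9%, a difference of 9.5 points.
- 0.7/0.9 becomes 0.91/0.97: 0.182/0.958 = 19.0% and 0.273/0.952 = 28.7%, a difference of 9.7 points.

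**6. Week 6.** A diary collected at week 2 cannot hold an answer given at week 6. Either another collection route exists and Table 2 omits it, or one of the two tables is wrong.

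**The case against.** **The article is condensed.** One sentence summarises a form that is not shown, and the full form may hold more questions. That is fair, and it is why the point concerns the form as described. It does not remove the point, because the sentence lists specific contents and Table 2 names no other source.

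**Selective return is conjecture.** This stands. The Background links unmet expectation to lower satisfaction, but nothing links satisfaction to diary return. The same section reports that the most effective strategies, CRP testing and shared decision making among them, cut prescribing without compromising satisfaction. The communication training is meant to elicit and address expectations, so satisfaction could even rise in those arms.

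**The planned model may be unaffected.** The Statistical analysis section plans multilevel logistic regression, with other error distributions according to the objective. For a binary item, step 3 leaves the odds ratio intact. This also stands, but only while the link between satisfaction and return is the same in every arm. Absolute rates and risk differences are distorted in either case.

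**Stronger readings that a reader might infer, and why they fail:**

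- *Dissatisfied patients drop out, which hides harm in the intervention arms.* No text supports the direction. Re-consultation, hospital admission and serious adverse events come from medical notes and do not depend on the diary. The protocol does not call the three items harm outcomes.
- *Non-returners have no record of other drugs.* Table 2 does name the diary for these, but the follow-up CRF includes current medications, and Table 1 schedules other drugs at day 1, week 2 and week 6.
- *The items are collected only in the diary.* Table 1's week 6 entry implies a further route or a conflict between the tables.

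**Conclusion.** The concern holds in a limited form. As described, patients who do not return the diary have no stated route to three secondary outcomes, and the week 6 source of those outcomes is unclear because Tables 1 and 2 do not agree. There is a risk of selective missing data, not a demonstrated bias. Under the assumed values, a 10-point difference shrinks by 1.3 to 2.4 points with an unchanged odds ratio; if return behaves differently by arm, the odds ratio moves in an unknown direction. All of these sizes rest on assumed dissatisfaction and return rates. No primary outcome is touched, so the priority is minor. It is worth acting on because the remedy is cheap and the missing answers cannot be obtained afterwards.

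**What to change.** 1. Add satisfaction with care, usefulness of the information and future consulting intentions to the telephone short form.
2. Record for each answer whether it came from the diary or the telephone.
3. Name the source of the week 6 assessment of these items, and bring Tables 1 and 2 into agreement.
4. Report diary return by arm.

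The cost is three short questions on a call already planned and a revision of the form. The downsides are a slightly longer call and a possible mode effect, since patients may answer more favourably by telephone than on paper. The source variable makes that effect visible in the analysis.

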### Resource use and costs

Micro-costing techniques will be used to estimate the healthcare costs for patients with acute cough in the different interventions. The costs will be presented in 2021 euros (year foreseen to finalize the study). Primary data of the ISAAC-CAT clinical trial will be used whenever possible. The costs will include the costs of treatment to control the acute cough and management of these patients. The cost of treatment will depend on the state of health of the patient but may include the costs of the different therapies prescribed, including those recommended to be purchased at the pharmacies. The costs of management will include the cost of primary care and secondary care visits within the first 6 weeks as well as any diagnostic tests performed and the number of days of patient absenteeism. The cost of the interventions will cover the continuous training, including the workshop and the monthly delivery of training microcapsules, the cost of the booklets, the cost of the CRP machine, and the reagents used.

### Cost-effectiveness and cost-utility analyses

The cost-effectiveness analysis will be conducted comparing costs and effectiveness/utility, measured in natural units and QALYs, respectively, of the different alternatives to usual practice. In most cases the data will be obtained from the ISAAC-CAT clinical study. The comparison will be performed using the incremental cost-effectiveness ratio and the incremental cost-utility ratio, defined as the ratio of the difference in costs and the difference in effectiveness or utility. The results will be expressed in terms of euros per unit of effectiveness.

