## Methods/design

### Objectives

This study aims to evaluate the effectiveness and efficiency of a continuous (workshop and monthly web-based training) disease-focused intervention (CRP testing) and a continuous (on-site and monthly online training) illness-focused intervention (enhancement of communication skills to optimise doctor-patient consultations and share decision making with the aid of patient-centred leaflets) on antibiotic prescribing in patients with ALRTIs in Catalan primary care centres. An economic evaluation of four strategies for reducing antibiotic prescribing will be performed. Particularly, a cost-effectiveness and cost-utility analysis will be conducted. These interventions will be compared with the current antibiotic prescribing strategy used in the primary care centres. The analysis will be conducted from the societal and the national healthcare system perspectives. Two qualitative studies (pre- and post-clinical trial) will be also conducted to inform the development and evaluation of the clinical trial.

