### Sample size calculation

To calculate the sample size, we will use a type I error of 5% and a power of 80%, and we will assume that antibiotic prescribing will decrease by at least 15%, from 60% to 45%, in any one of the three intervention groups. We will also assume a drop-out rate of 12% and an intra-cluster correlation coefficient for antibiotic prescribing within practices of up to 0.07, based on two recent studies [14, 16]. We estimate that a sample of 788 (197 × 4) patients will be needed. Allowance for an inflation factor of 3.73 due to clustering and rounding of numbers for the four subgroups give an overall sample size of 2940 [17]. As a consequence, at least 147 patients will be recruited per centre.

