### Trial interventions

The centres will be randomly assigned to four trial arms: usual care, training in the use of a point-of-care CRP test, training in enhanced communication skills, or combined training in CRP testing and enhanced communication skills (Fig. 1). Masking of GPs or patients to the intervention itself is not possible. Randomisation of primary care centres will be achieved by computer generation of random numbers.

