### Statistical analysis

Analyses will be carried out by intention to treat and will use multilevel logistic regression modelling with different distributions of errors according to the objective analysed for a factorial study controlled for the baseline antibiotic prescribing rate and with allowance for clustering by GP and health centre. The effects of various potential confounders related to clinical severity will be explored because of the potential for selection bias in an open trial. If interactions between interventions are not significant, the results will be presented as the main effects of each intervention (e.g., factorial groups with estimates controlling mutually for each intervention). The analysis will be performed using Stata 15 econometric software (StataCorp, College Station, TX, USA).

To study uncertainty, univariate and multivariate deterministic sensitivity analyses of the relevant parameters considered will be undertaken.

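### Usual practice is the only comparator named for the cost-effectiveness ratios, and ratios against it cannot show which of four mutually exclusive strategies is efficient

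*Protocol article*

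**What the plan says.** The Objectives section of the protocol article states: "An economic evaluation of four strategies for reducing antibiotic prescribing will be performed". It then names the comparator: "These interventions will be compared with the current antibiotic prescribing strategy used in the primary care centres".

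The section on cost-effectiveness and cost-utility analyses describes the comparison of costs and effects as "measured in natural units and QALYs, respectively, of the different alternatives to usual practice". The incremental ratio is "defined as the ratio of the difference in costs and the difference in effectiveness or utility", and results are to be given as euros per unit of effectiveness.

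Under Trial interventions, the arms are listed as "usual care, training in the use of a point-of-care CRP test, training in enhanced communication skills, or combined training in CRP testing and enhanced communication". A centre is therefore in exactly one of the four arms, and the fourth arm consists of the second and third together.

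No section mentions comparing the combined arm with a single intervention, ranking the strategies, removing dominated ones, or net benefit.

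**The concern.** When several options exclude one another, the efficient one is found step by step: each costlier option must justify its extra cost over the next less costly option that is still in contention. A ratio taken from usual care to the combined arm merges two steps, usual care to single and single to combined, into an effect-weighted average. If the first step is good value and the second is poor, the average can still look acceptable.

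The design makes this worth settling. Clinicians in the combined arm receive both training programmes (Trial interventions), and the costed items include training, booklets, the CRP machine and reagents (Resource use and costs). The Background cites two studies in which the combination gave the greatest reduction in prescribing. A combined arm that costs more and does somewhat better than a single intervention is thus plausible, and that is the pattern in which a usual-care comparator says least about the choice. At stake is the interpretation of the economic results; the clinical comparison is unaffected.

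**Working it through.** **Inputs.** The article gives no arm costs, QALY differences or willingness-to-pay threshold, so there is no planned figure to reproduce. Every euro, QALY and threshold value below is an assumption chosen to show the mechanism. The one document input is the planning assumption that prescribing falls by at least 15 percentage points, from 60% to 45%, in any one of the three intervention groups (Sample size calculation).

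**Formulas.** Ratio of strategy a against b = (cost a − cost b) / (effect a − effect b). Net monetary benefit = threshold × QALY gain − extra cost.

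**Step 1: an assumed case.** Per patient, against usual care:

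- Single intervention A: +EUR 20, +0.0020 QALY. Ratio 20/0.0020 = EUR 10,000 per QALY.
- Combined: +EUR 45, +0.0025 QALY. Ratio 45/0.0025 = EUR 18,000 per QALY.
- Combined against A: (45 − 20)/(0.0025 − 0.0020) = 25/0.0005 = EUR 50,000 per QALY.

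The averaging is visible: (0.0020 × 10,000 + 0.0005 × 50,000)/0.0025 = 45/0.0025 = 18,000.

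**Step 2: net benefit as a check.**

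| Assumed threshold (EUR per QALY) | A | Combined |
|---|---|---|
| 20,000 | 40 − 20 = 20 | 50 − 45 = 5 |
| 25,000 | 50 − 20 = 30 | 62.5 − 45 = 17.5 |
| 30,000 | 60 − 20 = 40 | 75 − 45 = 30 |

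Both strategies beat usual care at all three thresholds, and A is better than combined at all three.

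**Step 3: sensitivity to the assumed gain.** Keep the extra cost of combined over A at EUR 25. An extra 0.001 QALY gives 25/0.001 = EUR 25,000 per QALY; an extra 0.002 gives 25/0.002 = EUR 12,500. In the last case combined is preferred at every threshold used. On a grid of 144 assumed scenarios, A and combined both passed against usual care while combined failed against A in 38 (threshold 20,000), 36 (25,000) and 31 (30,000), that is 26%, 25% and 22%. These shares describe the grid; they are not probabilities for this trial.

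**Step 4: when the other single arm reveals the problem.** If costs and effects are additive, combined minus A equals the other single intervention B minus usual care. In step 1, B would then show +EUR 25 and +0.0005 QALY, a ratio of EUR 50,000 against usual care, so the poor step would be visible. Now suppose the effects overlap and B alone gives +0.0020 QALY for EUR 25. Its ratio is 25/0.0020 = EUR 12,500. All three ratios against usual care (10,000, 12,500 and 18,000) lie below 20,000, yet B is dominated by A (same effect, higher cost) and combined still costs EUR 50,000 per QALY over A.

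**Step 5: the planning effect.** If every intervention arm achieved exactly the 15-point minimum, combined would add nothing to A in antibiotic use avoided. At the assumed costs the ratios against usual care would be 20/0.15 = EUR 133 and 45/0.15 = EUR 300 per antibiotic-treated patient avoided. Both are finite, although combined is dominated on this outcome. The 15 points is a stated minimum, not a prediction for the combined arm.

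**The case against.** Several points on the other side have weight.

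- **The text does not exclude other comparisons.** A reader might infer that the plan restricts itself to usual care, or that it contains a rule by which the combined arm would be endorsed. Neither is supported: no sentence rules out further comparisons, and no threshold or adoption criterion is given. This stands.
- **The wording of the economic section is open.** Its phrase can be read as naming the three non-usual strategies and comparing them with one another, the ratio definition fixes no reference arm, and the reference to four strategies fits a four-way comparison. Taken alone, that is fair. The Objectives, however, state current practice as the comparator, and no other is named anywhere.
- **A condensed article leaves detail to a fuller plan.** Dominance steps may well be set out in a document not shown. That would be a full answer if the article were silent on the comparator, but it names one, and the one named does not settle the choice among strategies.
- **The factorial analysis may expose a poor component.** The article says "If interactions between interventions are not significant, the results will be presented as the main effects of each intervention". With additive costs and effects, step 4 shows that the single-arm ratio would reveal the problem. This stands in part: the statement depends on the interaction test and is not tied to costs or ratios. Sub-additive effects remove the protection.
- **Readers can subtract.** They can if cost and effect differences by arm are published; the ratios alone do not allow it.

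The uncertainty analysis does not change the position: "univariate and multivariate deterministic sensitivity analyses of the relevant parameters considered will be undertaken" concerns parameters and adds no comparator.

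**Conclusion.** The point holds in a limited form. The economic evaluation covers four mutually exclusive strategies, and usual practice is the only comparator the document names for the ratios. Those ratios are legitimate and answer whether each strategy improves on current practice. They do not identify the efficient strategy, and an acceptable ratio for the combined arm is compatible with poor value over a single intervention or with dominance.

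It would go too far to say that the plan would lead to the wrong choice. Whether the conclusion changes depends on costs and QALYs not yet known. In the assumed examples the ratio of combined over single ranged from EUR 12,500 to EUR 50,000 per QALY, on either side of the assumed thresholds. This is a worthwhile correction to the economic section, with no bearing on design, recruitment or the clinical outcomes.

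**What to change.** In the section on cost-effectiveness and cost-utility analyses, add wording to this effect: the four strategies will be ordered by mean cost; dominated and extendedly dominated strategies will be removed; and each remaining strategy will have its ratio reported against the next less costly one. Comparing net monetary benefit across all four arms, over a stated range of thresholds, is an equivalent alternative. Keep the ratios against usual care as supplementary results, and align the comparator sentence in the Objectives.

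The cost is about two sentences and a small amount of extra analysis on the same data. No new data or patients are needed. If a fuller economic plan already contains this step, it is enough to state it here.
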